## STUDY DESIGN

**Study Type:** Crossover clinical trial (interventional)

**Allocation:** Randomized

**Masking:** None (Open Label)

**Study Timeframe:** June 3, 2019 – June 28, 2019

This study takes place over four consecutive weeks for five days (Monday through Friday) for a total of 20 study days.

**Intervention/Treatment:** The primary intervention of interest is the time constraints during school meals, randomly assigning either 10 minutes or 20 minutes of seated lunch time to each study day.

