### Eligibility Criteria:

- Elementary and middle school-aged children attending a university summer camp
- Parent written consent to participate
- Children provide own assent to participate
- Children eat provided camp lunch

**Treatment Plan & Randomization:** Participants are served school lunches that met National School Lunch Program (NSLP) nutrition standards. Over the course of 20 study days, there are 10 days assigned to each lunch period: a) 10 minutes of seated lunch time and b) 20 minutes of seated lunch time. Five menus were served throughout the course of the study in order to provide variation to the lunches. Lunch time was randomly assigned within each menu so there is a total of two repetitions of each menu and lunch time.

Table 1. *Lunch time assignment and menu pairings\* by Study Day*

| Week: | Monday                     | Tuesday                    | Wednesday                  | Thursday                   | Friday                     |
|-------|----------------------------|----------------------------|----------------------------|----------------------------|----------------------------|
| 1     | June 3
A
10 minutes  | June 4
B
20 minutes  | June 5
C
10 minutes  | June 6
B
10 minutes  | June 7
D
20 minutes  |
| 2     | June 10
A
20 minutes | June 11
E
10 minutes | June 12
C
20 minutes | June 13
E
20 minutes | June 14
D
10 minutes |
| 3     | June 17
A
10 minutes | June 18
B
10 minutes | June 19
C
10 minutes | June 20
B
20 minutes | June 21
D
20 minutes |
| 4     | June 24
A
20 minutes | June 25
E
10 minutes | June 26
C
20 minutes | June 27
E
20 minutes | June 28
D
10 minutes |

\*There are 5 different menus (labeled A-E). Each menu was served 4 times over the course of the study, consisting of two menu-lunch time dyads occurring during the study period. The lunch time was randomly determined for the first and third occurring menu date, and the alternate lunch time was assigned to the second and fourth occurring date accordingly.

**Treatment Arms:** Due to logistics, there will be only one sequence of menu and length of lunch throughout the study.

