#### *Seated Lunch Time:*

Seated lunch time will be measured in two ways in this study. The first measure will be a categorical variable that indicates the randomly assigned seated lunch time: 10 minutes or 20 minutes. There will be a total of 10 10-minute days and 10 20-minute days throughout the study.

The second measure will use the actual time a participant is seated eating lunch. This continuous variable will be calculated using the actual observed seated lunch time. The total seated lunch time is calculated as the time a participant stood up at the end of lunch minus the time a participant sat down at the beginning of lunch. Additional non-seated time recorded on the observer sheet will be subtracted from this lunch time to account for time a participant may have gotten up after initially sitting down.

Inter-rater reliability was assessed for 27.4% of trays during the study that had multiple observers for the same participant. The inter-rater reliability for both the length of lunch and non-seated time had excellent agreement as measured by the intra-class correlation coefficient

- Observed length of lunch: 0.998 (95% CI: 0.997, 0.999)
- Non-seated time: 0.954 (95% CI: 0.888, 0.979)

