#### **Analysis Plan:**

*Descriptive statistics:* Descriptive statistics will include a count of participants and total trays, frequencies of categorical demographic information, and mean and standard deviation of continuous demographic information.

*Selection:* Percent of participants who select each food item overall and broken down by 10-minute and 20-minute seated lunch time. Chi square tests can compare the differences in selection distribution between 10-minute and 20-minute seated lunch time .

*Model parameters:* Mixed effects linear regression models will assess all continuous outcome measures and will include the following:

- Random effects: participants (to control for repeated measures)
- Fixed effects: menu (5 levels), prior menu exposure (4 levels), average talking rating, average phone use rating.

- For amount wasted and all nutrient models: an additional fixed effect of the reference weight/volume or reference nutrient (to control for variability of available food/nutrients pre-consumption)

For models that include the categorical time (10-minute and 20-minute seated lunch time), the estimated marginal means (emmeans) will be used to compare the mean outcome for 10-minute and 20-minute seated lunch time. The contrast between the means (10 minute-mean minus 20-minute mean) will also be reported along with a p-value. Models that used continuous time variable will assess the beta coefficient, t-value, and p-value. Beta coefficients will represent the change in outcome for a one minute increase in seated lunch time.

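### Lunch time is randomised to whole study days, but the mixed models carry only a participant random effect, so the 10- versus 20-minute contrast ignores residual day-to-day variation

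*Protocol*

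**What the plan says.** **Assignment.** Study Design describes the intervention as "randomly assigning either 10 minutes or 20 minutes of seated lunch time to each study day" and states that the study runs "for a total of 20 study days". The Seated Lunch Time section adds: "There will be a total of 10 10-minute days and 10 20-minute days throughout the study". The footnote to Table 1 gives the restriction: "The lunch time was randomly determined for the first and third occurring menu date, and the alternate lunch time was assigned". The alternate falls on that menu's second and fourth dates. Under Treatment Arms, "there will be only one sequence of menu and length of lunch throughout the study". Every child present on a given day therefore has the same assigned lunch time.

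**Analysis.** The Analysis Plan lists "Random effects: participants (to control for repeated measures") and "Fixed effects: menu (5 levels), prior menu exposure (4 levels), average talking rating, average phone use rating". The amount-wasted and nutrient models also adjust for the reference amount. For categorical time, the plan reports the difference in estimated marginal means with a p-value. No term stands for the study day or the menu pair, and the plan names neither a day-level variance estimator nor day-level degrees of freedom.

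**The concern.** A participant effect accounts for repeated trays from one child. It does not account for trays from different children at the same lunch, who share both the assigned time and whatever was particular to that day, such as how the food turned out, the weather or the mood of the group. Days are what was randomised, so this shared variation enters the time contrast in full. The planned standard error, however, treats trays as independent once child and the listed covariates are allowed for.

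At stake is the main inference for every continuous outcome with categorical time. An ordinary difference between two sets of 10 days could be reported as an effect of lunch length, because it is judged against variation between trays rather than variation between days.

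**Working it through.** **1. Reproduce the stated design.** Table 1 gives 10 ten-minute and 10 twenty-minute days, with two days in each menu-by-time cell. This agrees with the text. Taking each menu's dates in order gives the following pairs:

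| Menu | Dates 1 and 2 | Dates 3 and 4 |
|---|---|---|
| A | June 3 (10), June 10 (20) | June 17 (10), June 24 (20) |
| B | June 4 (20), June 6 (10) | June 18 (10), June 20 (20) |
| C | June 5 (10), June 12 (20) | June 19 (10), June 26 (20) |
| D | June 7 (20), June 14 (10) | June 21 (20), June 28 (10) |
| E | June 11 (10), June 13 (20) | June 25 (10), June 27 (20) |

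That makes 10 pairs, each with one day per condition and one random draw. The protocol has no sample size, power or alpha figure to reproduce.

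**2. Day-level degrees of freedom.** These depend on how the days are analysed:
- as 10 pairs: 10 − 1 = 9 (critical t 2.26);
- 20 days with menu and calendar-order exposure: 20 − 1 (intercept) − 1 (time) − 4 (menu) − 3 (exposure) = 11 (critical t 2.20);
- 20 days with menu only: 20 − 1 − 1 − 4 = 14 (critical t 2.14).

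**3. Size by formula.** Let m be trays per day and rho the day share of the within-child residual variance, given menu. Neither is in the protocol, and a nominal two-sided 5% is also assumed. With treatment constant within a day,

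true variance / planned variance ≈ (1 − rho) + m × rho,

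real alpha ≈ 2 × [1 − Φ(1.96 / √ratio)].

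| m | rho | Variance ratio | SE ratio | Real alpha |
|---|---|---|---|---|
| 10 | 0.01 | 0.99 + 0.10 = 1.09 | 1.04 | 6.0% |
| 10 | 0.05 | 0.95 + 0.50 = 1.45 | 1.20 | 10.4% |
| 20 | 0.02 | 0.98 + 0.40 = 1.38 | 1.17 | 9.5% |
| 20 | 0.05 | 0.95 + 1.00 = 1.95 | 1.40 | 16.0% |
| 20 | 0.10 | 0.90 + 2.00 = 2.90 | 1.70 | 25.0% |
| 40 | 0.05 | 0.95 + 2.00 = 2.95 | 1.72 | 25.4% |
| 40 | 0.10 | 0.90 + 4.00 = 4.90 | 2.21 | 37.6% |

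**4. Check by simulation.** Trials with no true effect were generated on the Table 1 calendar, 600 per cell. Children attended one to four weeks, with an assumed 50% chance of staying on each week. The child variance was set at half the within-child variance. The fitted model was a participant-only REML model with menu and each child's own prior exposure; talking and phone ratings were not simulated. Rejection rates at a nominal 5% were:

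| m | rho = 0 | 0.02 | 0.05 | 0.10 |
|---|---|---|---|---|
| 10 | 6.0% | 7.0% | 10.7% | 13.7% |
| 20 | 5.0% | 9.0% | 13.8% | 25.2% |
| 30 | 5.2% | 11.2% | 19.8% | 32.7% |

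With 600 runs, the Monte Carlo standard error near 5% is √(0.05 × 0.95 / 600) ≈ 0.9 percentage points. The simulated rates agree closely with the formula. On the same data, a t-test on the 20 day means adjusted for menu (14 df) rejected in about 3% to 5% of runs throughout.

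**The case against.** The strongest reply is that residual day variation may be small. Lunch time was randomised within menu and menu is a fixed effect, so differences between menus drop out. The protocol also standardises the day: same morning snack time, no physical activity before lunch, one indoor room, a 12:30 start and pre-portioned servings. Talking and phone ratings may absorb part of the group mood. All of this stands. It means that rho must be read as conditional on menu and could be low, but it does not make rho zero, and the planned model neither estimates it nor allows for it.

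Some stronger readings are tempting but are not supported:
- *All trays share the error of a mean-of-five reference weight.* Food Preparation has individually packaged items with larger weight variation weighed one by one. Amount wasted is a direct weight or volume of leftovers, and the reference amount is a covariate in the waste and nutrient models.
- *A slow line cuts into the assigned time.* The clock starts only when the last child has sat down.
- *Exactly 11 degrees of freedom apply.* That assumes prior exposure follows the calendar. The protocol does not define its coding, and children attending one to four weeks may differ in exposure on the same day.
- *Every model is affected equally.* Actual seated time varies between children within a day, so the continuous-time models are exposed to a lesser, unquantified degree.

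It could also be said that the matter belongs in an SAP. The method for degrees of freedom might. The random-effects structure is written out in the protocol, however, so it is a stated choice rather than a gap.

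**Conclusion.** The point holds for the categorical contrast in the percent-consumed, amount-wasted and nutrient models. Days were randomised, the model has no day term, and the p-value is too small whenever days with the same menu differ beyond what the covariates explain.

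The direction of the error is certain if rho exceeds zero, but its size is not. Over assumed ranges of m = 10 to 40 and rho = 0.01 to 0.10, real alpha runs from about 6% to about 38%, with 16% at m = 20 and rho = 0.05. A reader might take the upper figures as the trial's actual error rate. The protocol does not support that, because it states neither enrolment per day nor any day variance, and at the low end the inflation is slight. Nor does this point show that the estimated difference is biased or that a significant result would be false. It concerns the stated precision. An honest test of assigned lunch time rests on roughly 9 to 14 day-level degrees of freedom, not on the number of trays.

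**What to change.** Add a random intercept for study day, crossed with participant, to the mixed models in the Analysis Plan, and test lunch time with Satterthwaite or Kenward-Roger degrees of freedom. State that the day term stays in the model whatever its estimated variance, and report that variance. Define how prior menu exposure is coded, because the day-level degrees of freedom depend on it.

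As a check on the categorical contrast, report a re-randomisation test that swaps lunch times within the 10 menu pairs. There are 2^10 = 1,024 assignments, taking the draws as independent with equal chances. The smallest attainable two-sided p-value is 2/1,024 ≈ 0.002, so the test can still detect an effect.

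The cost is one variance term and one additional analysis. No new data are needed, since the study day of each tray is known. The price is wider confidence intervals, which will be only slightly wider if day-to-day variation proves small.

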## PROJECT SUMMARY

**Study Title:** Time for Lunch: The Impact of Seated Lunch Time Constraints on Child Eating Behaviors

**Sponsor:** United States Department of Agriculture Hatch Project #ILLU-698-315.

**Background and Significance:** Recent peer-reviewed observational evidence suggests that school children receive anywhere from 10-33 minutes of seated lunch time and that students with less time to eat discard higher amounts of milk, entree (i.e. protein items), grains, and vegetables. This waste is a missed opportunity for improved nutritional security and healthy habit development. The purpose of this study is to estimate the impact that lunch time constraints have on child food selection, consumption and waste behaviors using a crossover trial design, where seated lunch time is randomly allocated to be either 10 minutes or 20 minutes each day.

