## STUDY RECRUITMENT AND STUDY POPULATION

**Recruitment:** Study participants will be recruited from a university summer camp. All children who sign up for a university summer camp will be invited to participate in the study. Lunch will be provided for free to all children as a benefit, regardless of study participation. There were no additional incentives to participate in the study.

Parents will be sent information about the study, a consent form, and demographic form electronically when signing up for the summer camp. Parents can complete the consent form electronically or bring a hard copy the first day of camp. Parents will also fill out a demographic information form for their child along with the consent form. During the first day of camp, children will provide written assent to participate on the first day of camp each week.

Children can sign up for 1-4 weeks of camp and therefore were not expected to participate in every study day.

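### With participants as the only random effect, the standard error of the 10- versus 20-minute contrast is too small to the extent that children differ in their response to lunch time

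*Protocol*

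**What the plan says.** The Analysis Plan section of the protocol specifies linear mixed models for all continuous outcomes. The random part is one line: "Random effects: participants (to control for repeated measures". The fixed part is listed as "Fixed effects: menu (5 levels), prior menu exposure (4 levels), average talking rating, average phone use rating", with the reference weight, volume or nutrient added in some models. Lunch time enters either as two categories or as observed minutes. In the first case, "The contrast between the means (10 minute-mean minus 20-minute mean) will also be reported along with a p-value". In the second, a single coefficient per minute is reported. No participant-by-lunch-time term and no study-day term is listed.

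Three features of the design bear on this:
- **Replication.** The Treatment Plan & Randomization paragraph says that "there is a total of two repetitions of each menu and lunch time", and the Seated Lunch Time section says "There will be a total of 10 10-minute days and 10 20-minute days throughout the study".
- **Uneven attendance.** The recruitment section says "Children can sign up for 1-4 weeks of camp and therefore were not expected to participate in every study day".
- **Assignment by day.** The Study Design section describes "randomly assigning either 10 minutes or 20 minutes of seated lunch time to each study day", and the treatment plan adds that one sequence serves everyone.

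The aim in the Project Summary is to "estimate the impact that lunch time constraints have on child food selection, consumption and waste behaviors".

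**The concern.** A random intercept absorbs a child's general level of eating or waste, and it cancels when that child's 10-minute trays are compared with the same child's 20-minute trays. It says nothing about whether the difference between lunch times is the same for a slow eater and a fast one. If it is not, all of a child's trays at one lunch time share that child's own response. More days from the same child then do not average that variation away; only more children do. A model without the term treats each further tray as fresh information on the average effect.

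At stake is the precision claimed for the contrast on percent consumed, amount wasted and the nutrient outcomes, and likewise for the per-minute coefficient. The point estimates are not in question.

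**Working it through.** **There is no plan figure to reproduce.** The protocol states no sample size, variance or standard error. The one checkable count is correct: Table 1 has 3, 2, 3 and 2 ten-minute days in weeks 1 to 4, which is 10 of 20.

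**Inputs from the protocol.** The day-by-day menu and lunch time in Table 1; attendance of 1 to 4 weeks; menu and prior menu exposure as fixed effects. A fully attending child has 2 or 3 trays per lunch time in one week and 10 per lunch time in four.

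**Assumptions, not in the protocol.** 40 children; residual SD σ = 30 percentage points (pp); intercept SD 20 pp; SD of the child-specific lunch-time effect τ = 10, 15 or 20 pp. Prior exposure is counted per child. The talking and phone ratings are left out.

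**Step 1: a case that can be done by hand (all children attend four weeks).** Code lunch time as ±0.5. Its sum of squares over 20 days is 20 × 0.25 = 5. Each menu has two days at each lunch time, so adjusting for menu costs nothing. By exposure level, however, Table 1 has 3, 2, 4 and 1 ten-minute days out of 5. That removes 5 × (0.1² + 0.1² + 0.3² + 0.3²) = 1.0 and leaves 4. Per child:
- true variance of the contrast = σ²/4 + τ²
- variance the intercept-only model reports = (σ² + τ²/4)/4, because part of the spread in response is absorbed into the residual

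| τ (pp) | True variance | Model variance | True SE / model SE |
|---|---|---|---|
| 0 | 225 | 225 | 1.00 |
| 10 | 325 | 231.25 | 1.19 |
| 15 | 450 | 239.06 | 1.37 |
| 20 | 625 | 250 | 1.58 |

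**Step 2: other attendance patterns.** The same comparison by generalised least squares on the Table 1 design gives, for τ = 10/15/20:
- all one week: 1.05/1.10/1.16
- even mix of one to four weeks: 1.15/1.30/1.47

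Counting exposure by the camp schedule instead of per child gives 1.14/1.29/1.45 for the mix. A separate calculation with a within-child estimator at τ = 0.5σ gave model-to-true ratios of 0.92, 0.78 and 0.73 for one week, mix and four weeks, which invert to 1.09, 1.28 and 1.37. It found almost no dependence on the number of children (20, 40 or 80).

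**Step 3: what this does to an interval.** The coverage of a nominal 95% interval for the average effect is 2Φ(1.96/ratio) − 1. For the mix this is about 91%, 87% and 82%.

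**Step 4: is the extra term enough?** Now suppose that days also differ, with an assumed SD of 5 pp. Even mix, 40 children, true SE / model SE:

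| Random terms besides the intercept | τ = 10 | τ = 15 | τ = 20 |
|---|---|---|---|
| none | 1.38 | 1.50 | 1.64 |
| child lunch-time effect only | 1.21 | 1.16 | 1.13 |
| study day only | 1.09 | 1.19 | 1.32 |
| both | 1.00 | 1.00 | 1.00 |

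The last row is exact because the variance components are treated as known. With τ = 0 and the day effect unmodelled, the ratio is 1.27.

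**The case against.** **The protocol does not say intercept only.** True. Neither intercept nor slope is mentioned, and an analysis plan not shown here could add a slope. A reader might infer that the protocol expressly imposes one response on every child; it does not. But the protocol does set out its model term by term, and a bare participant effect beside a single contrast is ordinarily read as a random intercept. If a slope was meant, the same one-line edit is needed.

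**The understatement depends on a variance nobody has given.** This stands. A reader might infer that the standard error is wrong as a matter of fact. The documents support only the conditional statement: with τ = 0 the ratio is exactly 1.00, and every other ratio above rests on assumed values.

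**Inflated false-positive rates need an unusual null.** This also stands. The mix ratios convert to test sizes of roughly 9% to 18%, and a reader might take these as the trial's type I error. They apply only if the average effect is zero while individual effects are not. With mean 0 and SD 20 pp, about 31% of children would eat at least 10 pp less when given twice the time. If lunch time affects no child, the test runs at 5% in this respect. The loss of interval coverage needs no such null.

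**Heavier weight for long-stay campers is not an error.** Before menu adjustment, a four-week child carries 10 × 10/20 = 5.0 units of information and a one-week child 2 × 3/5 = 1.2, about four to one. Under a common effect that weighting is efficient, so it is no separate fault.

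**The target could be these campers only.** The spread in response would then not belong in the standard error in the same way. The stated aim does not settle this, but it sets no such limit, and a random participant effect already treats the children as a sample.

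**A slope alone does not give a valid standard error.** Correct, as Step 4 shows, and the fix has to reflect it.

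**Conclusion.** The point holds conditionally. On the usual reading of the Analysis Plan, the standard error of the lunch-time contrast is too small to the extent that children respond differently, and it is right if they do not. Under the stated assumptions and an even attendance mix, the true standard error is 1.15 to 1.47 times the reported one. The range is 1.05 to 1.16 if all attend one week and 1.19 to 1.58 if all attend four. The practical meaning is overconfidence about the average effect in children, not a demonstrated excess of false positives. It affects the continuous outcomes only. Omitting the term can only understate the uncertainty, and the data needed to estimate it are already collected, so the change is worth making. It must not be presented as sufficient, because assignment by whole day raises a separate dependence that it does not address.

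**What to change.** In the Analysis Plan, replace the single random term with:
- a participant intercept plus a participant-specific lunch-time effect: a random slope for 10 versus 20 minutes in the categorical models, and for observed minutes in the continuous-time models;
- a study-day random effect, since lunch time is assigned to whole days in one shared sequence.

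State that the participant slope is dropped only if its variance is estimated at zero. Take the standard error and degrees of freedom of the contrast from the model with both terms.

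The cost is two extra variance components per model and no new data. Intervals will be somewhat wider, and some fits will be singular, particularly where many children attend for one week with only two or three trays per lunch time. The stated fallback covers the participant slope.

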**Lunch Period:**

At the start of lunch, participants will form a line to enter the food serving area. Once participants are lined up, a research staff member will make an announcement about the length of seated lunch time for that day. Participants will retrieve their participant ID card and then move through the lunch line.

All food items will be pre-portioned, meaning there will be no option to select portion sizes of items. Children will be instructed to select menu items that qualify as a reimbursable lunch as defined by the National School Lunch Program. Thus, participants are required to select three different components and one must be a fruit or vegetable. (All entree items constituted two meal components: grain and protein). A researcher will check each participant's tray to ensure they have a reimbursable meal after exiting the serving line.

While selecting food items in the lunch line, participants will verbally ask for the food items they want, and research staff will serve the pre-portioned meal items (offer vs. serve format of the National School Lunch Program). Foods will be pre-portioned on small plates, food boats, or bowls. Food components that are hot will be served first due to the arrangement of the buffet equipment.

As participants exit the lunch line, a pre-consumption photo is taken of their selected food items. An ID card with the participant ID number will be included in each tray photograph.

Seated lunch time will officially begin when the last participant makes it through the line and sits down. At this time, a researcher will announce the exact time that lunch ends and will write the time on a poster. The researcher will make an additional announcement when five minutes remain for lunch.

Participants will not be allowed to get seconds on food items, however participants are allowed refills of water. Participants can also get up for condiments and utensils during lunch.

At the end of lunch, a final announcement is made for participants to walk their trays to the corner of the room to collect tray items for weighing.

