**Data Collection During Lunch Period:**

1. Meal component selection: a research staff member takes a photograph of each child's lunch to document selection (which meal component were chosen).
2. Line order: the number order of each child as they leave the survey line, as recorded by a research staff member and documented with a time stamp on the pre-consumption photos.
3. Seat layout: a research staff member documents where each participant sits at the study tables
4. Water refills: a research staff member documents all cups of water children get (unlimited refills were available), recording both the number of cups and the participant ID number.
5. Participant observations: at least one research staff member will observe each participant during lunch time to record information about: time a participant sits down, time a participant stands up, any additional time a participant is not seated in their chair, phone rating and talking during lunch, notes on any food that is spilled or traded, and other notes that may be helpful

during data analysis. *Note: some participants will have multiple observers to provide estimates of inter-rater reliability.*

6. Cover sheet: student researchers will fill out a cover sheet for each study day that includes information about weather and what time lunch started and ended each day.

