#### *Observed Social Behaviors:*

Talking and phone use ratings from the observer sheets will range from a scale of zero to five during the first part of lunch and the last five minutes. An overall rating during lunch will be calculated as the average of the rating for the first part of lunch and the last five minutes.

Inter-rater reliability was assessed for 32.8% of trays during the study that had multiple observers for the same student. The inter-rater reliability for both talking and phone use had excellent agreement as measured by the intra-class correlation coefficient:

- Talking: 0.954 (95% CI: 0.932, 0.967)
- Phone use: 0.967 (95% CI: 0.954, 0.976)

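### The randomised 10- versus 20-minute contrast is adjusted for talking and phone use rated during the same lunch, so it can differ from the total effect the trial sets out to estimate

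*Protocol*

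**What the plan says.** The aim in the Project Summary is to "estimate the impact that lunch time constraints have on child food selection, consumption and waste behaviors using a crossover trial design". The Study Design section describes the intervention as "randomly assigning either 10 minutes or 20 minutes of seated lunch time to each study day". No effect net of social behaviour is named as a target.

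On timing, the Lunch Period section has the children lined up before they are served, when "a research staff member will make an announcement about the length of seated lunch time for that day". The Food Preparation section likewise has them told on entering the room. Under Data Collection During Lunch Period, observers then record, among other items, "phone rating and talking during lunch". Under Observed Social Behaviors the ratings "will range from a scale of zero to five during the first part of lunch and the last five minutes", and "An overall rating during lunch will be calculated as the average of the rating for the first part of lunch and the last five minutes".

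The Model parameters paragraph of the Analysis Plan applies mixed linear models to all continuous outcomes and lists "Fixed effects: menu (5 levels), prior menu exposure (4 levels), average talking rating, average phone use rating". The reference weight, volume or nutrient is added for the waste and nutrient models. The contrast between the two lunch lengths, with its p-value, comes from the estimated marginal means of these models. The Protocol gives no reason for the two behaviour covariates and describes no model of the continuous outcomes without them.

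**The concern.** Both ratings are measured after assignment. Two routes could then make the adjusted contrast differ from the total effect.

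- **Mediator.** Lunch length may alter how much children talk or use phones, and that may alter how much they eat. Holding the ratings fixed removes that part of the effect.
- **Consequence of the outcome.** A child who has stopped eating is free to talk or use a phone, so a rating may partly record consumption. Conditioning on it then distorts the comparison even if lunch length has no direct effect on the rating.

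If either route operates, the reported contrast describes lunches with equal ratings, not the effect of giving children 10 rather than 20 minutes. This touches two of the three primary outcomes (percent consumed and amount wasted) and all nutrient outcomes. A larger sample would not remove the difference.

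**Working it through.** The Protocol states no effect size, standard deviation or power figure, so there is nothing of its own to reproduce. The order of events is documented; the sizes below are illustrative.

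**1. Order of events.** Lunch length announced, then food selected, then seated eating with talking and phone use rated, then waste weighed. Both ratings fall after assignment and alongside the eating that determines the outcome.

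**2. Mediator path.** Let T = 1 for 20 minutes and 0 for 10 minutes. Let the rating be M = aT + error and consumption be Y = cT + bM + error. The total effect is c + ab. The coefficient of T adjusted for M is c, that is, total − ab, so the shift is ab.

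Assumed inputs: total effect 10 percentage points (20 minus 10 minutes), a from 0 to 1.0 rating point, b from 2 to 5 percentage points per rating point in either direction.

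| a | b | ab | adjusted effect, 10 − ab |
|---|---|---|---|
| 0 | any | 0 | 10.0 |
| 0.25 | ±2 | ±0.5 | 9.5 or 10.5 |
| 0.5 | ±5 | ±2.5 | 7.5 or 12.5 |
| 1.0 | ±5 | ±5.0 | 5.0 or 15.0 |

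The shift runs from 0 to 5 percentage points either way. It does not depend on the assumed total of 10.

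**3. Reverse path.** Let Y = total × T + error with residual variance s², and M = aT + bY + error with residual variance 1. Here b is rating points per percentage point eaten. The adjusted effect is total − [b·s² / (b²·s² + 1)] × (a + b·total). Assumed: total = 10, SD = 25, so s² = 625.

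- a = 0, b = 0.01: 10 − (6.25/1.0625) × 0.1 = 9.4.
- a = 0, b = 0.04: 10 − (25/2) × 0.4 = 5.0.
- a = 0.5, b = 0.01: 10 − (6.25/1.0625) × 0.6 = 6.5.
- a = 0.5, b = 0.04: 10 − (25/2) × 0.9 = −1.25.
- a = 0.5, b = −0.02: 10 − (−12.5/1.25) × 0.3 = 13.0.

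The value b = 0.04 is strong: it implies 0.04 × 100 = 4 points of a 0–5 scale between eating nothing and eating everything. It marks an extreme, not an expectation.

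**4. Simulation check.** With 400,000 simulated records per scenario, least squares agreed with both formulas. The comparison without the rating returned 9.85 to 10.20 in every scenario, against the assumed total of 10.

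**5. How the rating is built.** The overall rating weights the two windows equally, but the last five minutes are 5/10 = 50% of a 10-minute lunch and 5/20 = 25% of a 20-minute lunch. Suppose ratings track time within each window, and a child is quiet (rating 1) for 8 minutes and then talks (rating 4).

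- 10-minute lunch: first part 1; last five minutes (3×1 + 2×4)/5 = 2.2; average (1 + 2.2)/2 = 1.6.
- 20-minute lunch: first part (8×1 + 7×4)/15 = 2.4; last five minutes 4; average (2.4 + 4)/2 = 3.2.

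The same behaviour by the clock can thus give different covariate values at the two lunch lengths.

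**6. Menu balance.** Counting Table 1, each of the five menus appears twice at 10 minutes and twice at 20 minutes, 10 days each. The ratings are not needed to repair an imbalance in menu.

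**The case against.** The strongest reply is that neither mechanism is documented. The covariate is an average of two 0–5 ratings, not minutes of talking, and the scale anchors are not given, so a longer lunch need not raise it. Nothing in the Protocol says that children talk or use phones once they have finished. If lunch length does not change the ratings, the mediator path gives no shift. This stands: the timing is certain, but the existence, direction and size of any bias are not.

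Second, the models using observed seated minutes have a non-randomised exposure, and talking or phone use could confound it. Adjustment there is defensible. This also stands.

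Third, the ratings might absorb day-to-day differences in social atmosphere, since attendance varies by week and seating is free. Assignment is also by day in a single sequence, with lunch length drawn at random only for the first and third date of each menu. Chance differences between days are therefore possible. That supports looking at an adjusted model, but it does not make a post-assignment covariate suitable for the main contrast.

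Fourth, an unseen SAP may add a model without the ratings. It may, but the Protocol itself fixes the adjusted model as the source of the reported contrast. The high inter-rater agreement reported for the ratings does not answer the point either: it shows that observers agree, not that the covariate is safe to adjust for.

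**Conclusion.** The point holds for the randomised 10- versus 20-minute contrast in percent consumed, amount wasted and nutrients. That contrast is conditioned on behaviour rated after assignment, so it can differ from the total effect in the stated aim, in either direction. By the mediator path the shift is 0 to 5 percentage points either way, under assumed rating shifts of 0 to 1.0 point and slopes of 2 to 5 percentage points per rating point. The reverse path could be larger or smaller and rests equally on assumption.

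A reader might infer more: that the contrast is certainly biased, that a non-zero shift has been shown, or that the ratings must leave every model. The documents support none of these. They contain no data linking lunch length, ratings and intake, and the observed-time models raise a different question. Selection, the third primary outcome, is compared by chi-square without covariates and is untouched.

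**What to change.** For the models with categorical lunch time, make the model without the talking and phone ratings the primary analysis. It keeps lunch time, menu, prior menu exposure, the reference value where already specified, and the participant random effect. Analyse the two ratings as outcomes of lunch time, which would also show whether they differ between the lunch lengths. Report the rating-adjusted model as exploratory and label it so.

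Leave the observed-seated-time models free to keep the ratings as possible confounders, and leave the chi-square selection tests as they are. Any other change to the random-effects structure is a separate matter and is not argued here.

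No new data are needed. The cost is a possible small loss of precision, if the ratings explain residual variation.
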